## Qualitative Method:

A semi-structured interview guide will be used at the 8-week post-randomization visit. Interviews will be audio-recorded and transcribed verbatim for subsequent analysis. The following key questions will be asked during the interview:

--> how important were e-ciagrettes/patch to you in helping you quit (what aspects)?

--> if attempting to quit again, what technique would you try and why?

--> how important was telephone counselling to you in helping you quit (what aspects)?

--> what was the most difficult challenge in quitting (what helped you overcome it)?

--> Do you smoke non-tobacco products (e.g. marijuana)? How does this effect your quitting smoking?

If not quit:

--> how interested are you in quitting now? (why this may or may not be a good time to quit)

--> how interested would you be in trying to quit another time? (why this time is preferred)

What benefits do you think you got/will get from quitting around the time of surgery?

What did you do when you had a craving to smoke a cigarette?

For e-cigarette group:

Did you use e-cigarettes and conventional cigarettes on the same day?

What made you want to use e-cigarettes versus conventional cigarettes? (what do you smoke now?)

How was this quit attempt different/similar to previous quit attempts?

Did you use non-study e-cigarette products?

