We plan to carry-out a pilot randomized controlled trial with parallel design comparing e-cigarettes and telephone counselling with transdermal nicotine replacement and telephone counselling. Our primary outcome is smoking cessation on the day of surgery, as confirmed biochemically by exhaled carbon monoxide. Smoking reduction (self-reported cigarettes per day) of 50% or more and bedside spirometry readings will be assessed as secondary outcomes.

**» Aim 2) To determine the acceptability of e-cigarettes amongst veterans as an aid for smoking cessation and to determine the feasibility of recruitment, randomization, and follow-up procedures in preparation for large-scale trial.**

Through implementation of this pilot trial, we will determine the feasibility and acceptability of e-cigarettes for smoking cessation perioperatively in the veteran population and obtain the preliminary data necessary to run a larger trial on the effectiveness of e-cigarettes as a perioperative smoking cessation aid.

**» Aim 3) To determine the safety of e-cigarettes as a harm reduction strategy to achieve short-term perioperative smoking cessation.**

We plan to improve the overall knowledge of the safety of short-term e-cigarettes use through careful surveillance for adverse events and side effects.

**» Aim 4) To determine if e-cigarette use preoperatively is associated with a lower risk of complications postoperatively.**

We plan to measure the following secondary outcomes: postoperative complications and mortality within the first 30 days, post-anesthesia care unit (PACU) length-of-stay, and hospital length-of-stay. This will help us understand if e-cigarettes have the potential to be used for harm-reduction perioperatively.

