## Qualitative Analysis:

Individual interviews will be performed 8-weeks after randomization to determine patient attitudes towards e-cigarettes and nicotine patches perioperatively. Specifically, we will solicit information from patients regarding their perceptions of how the intervention (e-cigarette or nicotine patch) affected their willingness and/or success at quitting. Thematic and content analysis will be used to identify core concepts and to develop categories for coding interview data. Content analysis will be used to systematically sort and code information based on themes.

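### The 8-week interview guide uses leading prompts and never asks what participants disliked or why they stopped or did not use the product, so the qualitative part of Aim 2 may miss why a product was unacceptable

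*Protocol*

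**What the plan says.** Aim 2 is, in part, "To determine the acceptability of e-cigarettes amongst veterans as an aid for smoking cessation". The Protocol approaches this in two ways.

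- **Quantitative.** The Outcomes section names satisfaction and use of the intervention at 8 weeks as the acceptability outcomes. The Statistical analysis plan section measures them with 0-7 agreement items and a frequency-of-use item whose lowest category is no use at all.
- **Qualitative.** A semi-structured interview is held at the 8-week visit. The Qualitative Analysis section gives its purpose as learning participants' "perceptions of how the intervention (e-cigarette or nicotine patch) affected their willingness and/or success at quitting", by thematic and content analysis.

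The Qualitative Method section states that the listed key questions will be asked. They include:

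- on the product: "how important were e-ciagrettes/patch to you in helping you quit (what aspects"
- on counselling: "how important was telephone counselling to you in helping you quit (what aspects"
- on difficulties: "what was the most difficult challenge in quitting (what helped you overcome it"
- on benefits: "What benefits do you think you got/will get from quitting around the time of surgery"
- for those who have not quit: "how interested are you in quitting now? (why this may or may not be a good time to quit", followed by a similar question about quitting at another time
- an open question: "if attempting to quit again, what technique would you try and why"

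The e-cigarette group is also asked what drew them to e-cigarettes over conventional cigarettes, and about same-day use of both, comparison with earlier quit attempts, and use of non-study products.

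**The concern.** The stated purpose is neutral: the product may have raised, lowered or not changed a person's willingness or success. The prompts are not neutral. They ask how the aid helped, what overcame the difficulty, what the benefits were, and what made e-cigarettes attractive. A participant who disliked the product, gave it up after a few days or never opened it is not asked to say so or to explain.

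That participant's account is especially useful to a pilot that is meant to inform a larger trial. Reasons for stopping can be foreseen: the section on the safety of the study e-cigarette describes a user of the same product type who discontinued because of throat irritation. If such reasons, or non-medical ones such as taste or inconvenience, are not drawn out at 8 weeks, no later contact is planned to recover them. The 6-month assessment covers self-reported smoking status and dual use only.

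**Working it through.** No estimate or test depends on this point, so the check is mainly a reading of the listed questions against their purpose.

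**1. Count of listed questions (Qualitative Method).** Opening block 5 (product, technique for another attempt, counselling, challenge, non-tobacco products); not-quit branch 2; general 2 (benefits, cravings); e-cigarette group 4. Total 5 + 2 + 2 + 4 = 13. The layout does not show where the not-quit branch ends, so the two general questions could be read as part of it. The total and the conclusion are the same either way.

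**2. Direction of the wording.**

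| Question | Frame | Invites a negative account of the product? |
| --- | --- | --- |
| Product | the aid helped the person quit | Only if the participant volunteers it |
| Counselling | same frame | Not about the product |
| Challenge | difficulty in quitting; the probe assumes it was overcome | Not about the product |
| Benefits | benefits only | No |
| Why e-cigarettes over cigarettes (e-cigarette arm) | reasons in favour only | No |
| Not-quit branch (2) | interest in quitting now or later | No |
| Technique for another attempt | open | Indirectly: another method may be preferred and explained |
| Remaining five (non-tobacco products, cravings, dual use, earlier attempts, non-study products) | neutral | Not directly |

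The rows account for 1 + 1 + 1 + 1 + 1 + 2 + 1 + 5 = 13 questions. Those asking directly about dislikes, or about reasons for stopping or non-use: 0 of 13.

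**3. Can another instrument supply the reason?**

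- The satisfaction item and its companions on helpfulness and recommendation give a rating, not a reason.
- The use item records how often the product was used, down to not at all, but not why.
- The safety questions (Adverse events section) are open-ended and checklist-based, and would pick up side effects. They are there for safety and need not capture non-medical reasons for rejecting a product.

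**4. How many participants this could concern.** The Protocol gives no expected 8-week quit rate. The Sample size section cites control-group quit rates of 4% to 65% in earlier perioperative studies, without a time point. Taking that range as an assumption for all 30 participants, and assuming all are interviewed:

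- at 65%: 30 × (1 − 0.65) = 10.5
- at 4%: 30 × (1 − 0.04) = 28.8

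So roughly 10 to 29 interviews could be with people who have not quit. This shows how many people may be asked success-framed questions. It does not measure bias.

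**5. The stated acceptability figure is unaffected.** The Sample size section claims 80% power for an effect of 1.085 on the satisfaction scale, with SD 1.0, 20 versus 10 participants and alpha 0.05 (taken as two-sided). By the normal approximation the detectable difference is (1.960 + 0.842) × √(1/10 + 1/20) = 2.802 × 0.3873 = 1.085, which reproduces the figure. It rests on the satisfaction rating and does not involve the interview.

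**The case against.** The best case against the point is that it concerns wording in a supplementary interview within a 30-person pilot, and that the guide is more open than it looks. Several parts of that case stand.

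- A reader might infer that the guide assumes throughout that the participant quit. It does not. There is a not-quit branch, the benefits question allows for benefits still to come, and difficulty in quitting can describe a failed attempt. A question about importance can be answered with none at all, and the open question on technique lets a participant turn away from the product and explain.
- A reader might infer that the Aim 2 acceptability evidence as a whole leans positive. The documents do not support that. The prespecified acceptability outcomes are the ratings and the use item, which can record full disagreement and complete non-use. Aim 2 also covers the feasibility of recruitment, randomization and follow-up.
- A reader might infer a tilt towards e-cigarettes over patches. The lead product question is the same in both arms, so it does not by itself favour either. Only the e-cigarette group's question on reasons for choosing e-cigarettes is one-sided.
- A reader might extend the criticism to the rating items or to their order relative to the interview. Only the satisfaction statement is given in full, a positive statement on an agreement scale is not an error, and no order is stated.

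A semi-structured format also permits unlisted probes. That is true, but none on dislikes or non-use is planned, so whether these are covered would depend on the interviewer. None of these arguments supplies the missing question, and the not-quit branch does not ask about the product.

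**Conclusion.** The point holds for the qualitative component only. The product, counselling, challenge-probe and benefits wording is leading, the e-cigarette arm is asked only for reasons in favour, and 0 of the 13 listed key questions ask what was disliked or why the product was stopped or not used. The interview therefore matches its neutral stated purpose poorly and may miss why a product was unacceptable, which the ratings and the use item cannot supply.

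The size of any distortion cannot be calculated from the Protocol. The prespecified quantitative acceptability outcomes, the power statement and all other stated figures are unchanged. The conclusion assumes that the listed questions are put as written and that no unlisted probes fill the gap. It is a modest design weakness, worth correcting because the correction is cheap and the lost information has no later planned collection.

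**What to change.** Revise the guide before the first 8-week interview:

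1. Reword the product and counselling questions neutrally in both arms, for example: *What part, if any, did the e-cigarettes or patch play in your quit attempt?* and the same form for counselling.
2. Ask about benefits or downsides, not benefits alone.
3. Add, in both arms: *What did you dislike about the product?* and *If you stopped or did not use it, why?*
4. Ask the e-cigarette arm also what made them choose conventional cigarettes over e-cigarettes.
5. In the not-quit branch, ask what got in the way.

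The cost is a few more minutes per interview and the corresponding transcription and coding. No extra visit or staff is needed, and the rating items, analyses and sample size stay as they are.

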## Sample size estimation:

Previous perioperative studies have shown an absolute difference in smoking cessation rates between intervention and control groups to be 13-76%, with quit rates in the control groups ranging from 4-65%[^4-7^](#_ENREF_4). The proposed sample size is 30 (20 intervention, 10 control), balancing cost against precision, as is conventional for a pilot study. We realize that since the sample size is small, between-group differences may not be statistically significant. However, the proposed sample size will provide rough estimates of Aim 1 (smoking cessation) and Aim 4 (postoperative complications) treatment effects, residuals, and within-subject correlations needed for the full-scale trial. The sample size will also establish the acceptability of the intervention (Aim 2). In order to proceed with a full trial assigning ENDD use to a larger number of veterans, we would like to determine from this pilot study if ENDD is more acceptable to patients than NRT, as reported in previous qualitative studies[^11^](#_ENREF_11). The proposed sample size will have 80% power to detect an effect size of 1.085, accepting an alpha of 0.05 and assuming the standard deviation of a likert scale (0-7) of satisfaction with the intervention (ENDD or NRT) is around 1.0[^37^](#_ENREF_37). Even if we are underpowered to see smaller differences, the point estimates and confidence intervals will provide rough estimates that will be useful in planning a future study.

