**Secondary outcomes:**

1. Descriptive outcomes of proportion of veterans eligible for inclusion, reasons for exclusion, and proportion of eligible veterans consenting to participate. Acceptability outcomes of satisfaction and use of intervention (any versus continuous) 8-weeks after randomization.

2. Smoking status at 8-weeks after randomization, as confirmed by exhaled CO.

3. Smoking reduction on the day of surgery and at 8-weeks after randomization (defined as 50% or less of baseline cigarettes smoked per day). Dual use of e-cigarettes and conventional cigarettes will also be assessed.

4. Bedside spirometry FEV1 (forced expiratory volume in first second), FVC (forced vital capacity), and cotinine level at 8-weeks after randomization (compared to baseline).

5. Postoperative complications or mortality within 30-days (by telephone self-report + chart review)

6. PACU length-of-stay

7. Hospital length-of-stay

8. Long-term assessment at 6 months - self-reported smoking status, including dual use of e-cigarettes.

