## Randomization and blinding:

After collection of baseline data, randomization will be done by computer-generated scheme with randomly permuted block sizes of 3 or 6 in a 2:1 fashion. Allocation will be concealed by consecutively numbered, sealed, opaque envelopes. Due to the nature of the intervention, blinding of subjects is not possible. whenever possible, healthcare providers will be blinded throughout the perioperative period. However, patients may report being in the study to their providers, which may inadvertently cause unblinding. Outcome adjudicators will be blinded.

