## Statistical analysis plan:

Descriptive statistics to assess feasibility:

-proportion ineligible for inclusion (95% CI by bionmial exact) and reasons for exclusion

-proportion of eligible veterans declining to participate (95% CI by binomial exact)

Baseline characteristics to be collected prior to randomization: age, gender, race/ethnicity, comorbidities (hypertension, coronary artery disease, chronic obstructive pulmonary disease, diabetes mellitus, other cardiac disease), scheduled surgical procedure and subspecialty, smoking habits (number of cigarettes per day, years smoking), Fagerstrom score for nicotine dependence. Operative day information to be collected in addition to outcomes listed below: surgical procedure, duration of surgery, anesthesia type (local/monitored anesthesia care/regional/general/combined)

| **Outcome** | **Data Description** | **Likely Distribution** | **Hypothesis Test** |
| --- | --- | --- | --- |
| Smoking cessation (primary outcome) | Proportion | n/a | Fisher’s exact test |
| Smoking reduction | Proportion | n/a | Fisher’s exact test |
| Smoking amount | Cigarettes/day, Continuous  Median (IQR) | Normal or skewed (plot histogram) | Normal: two-sided t-test  Skewed:Wilcoxon rank-sum |
| Unanticipated hospital admission | Proportion | n/a | Fisher’s Exact Test |
| Hospital length of stay | Days  Continuous  Median (IQR) | Skewed | Time-to-event using Cox proportional hazards model; graph Kaplan-Meier plot |
| 8-weeks after randomization: Agreement to (0-7 likert) "I was satisfied with product I was given (e-cigarette or patch) to help me quit" (and similar questions regarding how helpful they found it, and whether they would recommend e-cig/patch) | Likert 0-7, Ordinal, Median (IQR) | Skewed | Wilcoxon rank-sum |
| 8-weeks after randomization: During the 6-weeks after you entered the study, how often did you use the product you were given (e-cigarettes or patch)?  Everyday, most days, a few times a week, once a week, less than once a week, did not use at all | Proportion that used everyday Proportion that did not use at all. | n/a | Fisher’s exact test |
| Change in FEV1, FVC, salivary cotinine | Liters, Continuous (Mean, SD) | Normal | Paired t-test |
| Composite of 30-day postoperative complications and mortality | Proportion | n/a | Fisher’s Exact Test |
| Duration in PACU | Hours  Continuous  Median (IQR) | Skewed | Time-to-event using Cox proportional hazards model; graph Kaplan-Meier plot |

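### The stated 80% power at an effect size of 1.085 is a large-sample z figure; a t-test gives 77%, and the power of the planned Wilcoxon test depends on a score distribution the protocol does not fix

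*Protocol*

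**What the plan says.** The protocol's section on sample size estimation sets the total and the split: "The proposed sample size is 30 (20 intervention, 10 control), balancing cost against precision". The 2:1 ratio is repeated under randomization and blinding ("randomly permuted block sizes of 3 or 6 in a 2:1 fashion"). The power claim follows: "The proposed sample size will have 80% power to detect an effect size of 1.085, accepting an alpha of 0.05", "assuming the standard deviation of a likert scale (0-7) of satisfaction with the intervention (ENDD or NRT) is around 1.0". That section names neither the test nor whether alpha is one- or two-sided.

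The outcome table in the statistical analysis plan section describes and tests the satisfaction score as "Likert 0-7, Ordinal, Median (IQR) | Skewed | Wilcoxon rank-sum". The score is collected late; the secondary outcomes list has "Acceptability outcomes of satisfaction and use of intervention (any versus continuous) 8-weeks after randomization". The section on maximizing adherence offers a $40 incentive for completing the study. No expected completion rate is given, and the power sentence uses all 30 participants.

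**The concern.** An effect size quoted to three decimals implies a definite calculation, so one can ask which test it belongs to. The value 1.085 matches a formula that treats the SD as known, which is optimistic for groups of 20 and 10. The test in the outcome table is a different one again. A power figure should describe the planned analysis on the people expected to provide data, and this one does neither.

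What is at stake is interpretation. The protocol says it wants to learn, before a full trial, whether e-cigarettes are more acceptable than patches, and this is the one comparison for which it claims power. A null satisfaction result would be read against a claimed 80%, and the planners of the next trial may carry the figure forward.

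**Working it through.** **Inputs.** From the sample size section: n = 20 and 10, alpha 0.05, power 80%, effect 1.085, SD about 1.0. From the outcome table: Wilcoxon rank-sum test, score expected to be skewed. Two-sided alpha is my assumption, tested in step 1. The loss rates in step 4 are also assumptions, since the protocol gives none.

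**1. Reproducing the stated figure.** Detectable difference by the two-sided normal formula:

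(1.960 + 0.842) × √(1/20 + 1/10) = 2.802 × 0.3873 = 1.085.

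Power at 1.085 by the same formula is 79.996%. Two alternatives do not give 80%: a one-sided z calculation gives 87.6%, and 15 v 15 (two-sided z) gives 84.4%. The source of the figure is therefore clear.

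**2. The t-test with the same inputs.** Degrees of freedom 28, critical value 2.048, non-centrality 1.085 / 0.3873 = 2.801. Power from the non-central t distribution is 77.2%. For 80% the difference must be 1.124 SD.

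**3. The planned Wilcoxon test, 20 v 10, full follow-up.** Simulation, 20,000 runs per scenario, two-sided 0.05. Ranges cover the test with and without continuity correction.

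| Score distribution (SD about 1.0, difference about 1.085 unless noted) | Power |
| --- | --- |
| Continuous normal | 72-74% |
| Roughly symmetric integer scale, observed SD 1.0 | 74-76% |
| Reflected gamma, shape 8 | 77-79% (rounded to integers 75-76%) |
| Reflected gamma, shape 4 | 80-82% (rounded 78-79%) |
| Reflected gamma, shape 2 | 85-86% (rounded 79-80%) |
| Bounded 0-7 score, moderate skew (realised difference 1.11) | 79% |
| Bounded 0-7 score, strong skew (realised difference 1.13) | 88% |

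The last two rows run slightly high because the realised difference exceeded 1.085.

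A latent normal score with SD 1.0, rounded to 0-7 with a control mean of 3 to 5.5, gave 69-72%, and 65-66% with a control mean of 6. These do not match the protocol's assumption. Rounding adds about 1/12 to the variance, so the observed SD becomes √(1 + 1/12) = 1.04 and the standardised effect falls to 1.085 / 1.04 = 1.04. Near the ceiling, clipping shrinks the difference as well. The protocol sets the SD of the score itself at about 1.0, so I do not rely on these figures.

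**4. Sensitivity to loss by week 8 (assumed rates), effect 1.085.**

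| Evaluable | t-test | Wilcoxon, normal scores |
| --- | --- | --- |
| 20 v 10 | 77.2% | 72-74% |
| 18 v 9 (10% lost) | 72.4% | 68-69% |
| 16 v 8 (20% lost) | 66.8% | 62% |

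At 18 v 9 the skewed bounded scores also lost power: from 79% to 73-74% under moderate skew, and from 88% to 84-85% under strong skew.

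**The case against.** The strongest reply is that the protocol itself expects a skewed score. The Wilcoxon test is somewhat weaker than the t-test on normal data but often stronger on skewed data. In the skewed scenarios its power was below, at or above 80%, and an exponential shape took it to 91%. This stands. A reader might infer that the planned test falls short of 80% in every case, or that its power is simply 70-74%. The documents do not support either reading, because both need near-normal scores. For the same reason a flat statement that the test needs about 1.2 SD for 80% power should not go into the protocol.

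The second reply is that little hangs on the figure, and this also largely stands. Satisfaction is a secondary outcome. The total of 30 was set by cost and precision, not by this calculation. The protocol concedes that differences may not reach significance and that smaller effects are beyond its power. A reader might infer that the comparison decides whether a full trial goes ahead, but the protocol states only a wish to learn the answer and sets no threshold or rule. The shift from 1.085 to 1.124 is 0.04 SD, against an SD given only as approximate. The loss rates are assumptions and show sensitivity, not an error in the document.

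What these replies do not do is rescue the 80%. It was not derived from a skewed model, and the protocol specifies no distribution that would yield it. The concession about smaller differences covers effects below 1.085, not the claim made at 1.085.

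**Conclusion.** The point holds, at minor severity. The 80% is a two-sided z approximation for 20 v 10. The small-sample t-test gives 77% and reaches 80% at 1.12 SD; this needs only the protocol's own inputs, two-sided alpha and the t-test's usual normality assumption. The stated figure is also not the power of the planned Wilcoxon test. That is about 72-75% if scores are near normal and about 75% to the high 80s in the tabulated skewed scenarios, so it cannot be given as one number until a distribution is stated. Making no allowance for loss by week 8 is a further optimistic element: any loss lowers power, to about 72% (t-test) or 68-69% (Wilcoxon, normal scores) if 10% are lost. None of this shows that the pilot is the wrong size.

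**What to change.** Keep 30 participants and the Wilcoxon test. Replace the power sentence with one that names the two-sided test, the assumed score distribution and the number expected to be evaluable at 8 weeks. For example:

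> With 20 and 10 evaluable at 8 weeks, two-sided alpha 0.05 and an SD of 1.0, a t-test has 80% power for a difference of 1.12 (77% at 1.085). The planned Wilcoxon test has about 72-75% power at 1.085 if scores are near normal; this may differ if scores are skewed, and power is lower with any loss to follow-up.

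If the investigators can justify a particular skewed distribution, they should state it and give the simulated power for that case instead. The cost is one sentence and a slightly less favourable figure. Sample size, test and conduct do not change.
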